#### Nevi distribution characteristics

Implemented within the Canfield VECTRA DermaGraphix software, a Convolutional Neural Network (CNN) offers the probability assessment for each lesion, indicating the likelihood of it being a nevus. This algorithm was trained using ratings from an expert dermatologist as the gold standard (13). In addition, the longest diameter and 3D spatial coordinates of each lesion are calculated. For this study, all lesions with a diameter ≥ 3 mm with a nevus confidence >0.8 were considered nevi. This enables overall nevus count for the patient, as well as nevus distribution across anatomic sites.

#### Skin color measurement

Average skin color can be automatically measured across the 3D TBP image as the individual topography angle (ITA), calculated in the L*a*b* color space. A recent study in a highly sun-exposed population showed that most people had no photodamage on their lower torso and lower back third (26). Therefore, to calculate innate skin color the average of the non-lesion skin color from these locations is calculated. To estimate facultative skin color the average non-lesion skin color is calculated for the dorsal side of lower arms. The L* and b* values may be adjusted using a regression equation if it results in higher agreement with gold standard colorimeter values.

### Algorithm development

Algorithms will be developed to apply automatic annotations on previously unseen images acquired with the VECTRA WB360 and identify evolving changes in a patient’s skin images over time. Task specific algorithms include lesion detection and segmentation on the image tiles, inter-exploration lesion-matching, ugly duckling detection, classification of the detected lesions, intra-exploration lesion matching and lesion change detection. From the results of these algorithms, imaging phenotypes to compute the lesion risk assessment are extracted.

#### Data splitting

The annotated image tiles are divided into three distinct datasets (training, validation, and test datasets), for AI-based model development and evaluation process. This allocation ensures that the models are trained on a substantial portion of the data (training set), evaluated and tuned based on the validation subset, and ultimately tested on unseen data (test set) to estimate its real-world performance accurately.

The methodology employs a stratified randomization technique with 65% of the data allocated to the training set, 20% to the validation set, and the remaining 15% to the test set. Stratification is used to ensure all diagnostic classes (Table 1) are sufficiently represented in each dataset. This is vital to prevent potential class imbalances that could adversely affect the models’ performance and generalization.

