## Objectives

### Primary objective

The first objective is to build a database comprising skin images enriched with annotations related to skin lesion diagnostic categories, skin phenotype information, and patient-level metadata. This dataset aims to facilitate the development of algorithms tailored for both lesion-specific and patient-level risk assessment for melanoma. This master dataset will be partitioned to create separate training, test, and validation datasets.

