#### Sample size

Optimal sample sizes for AI-based image classification tasks are difficult to estimate. Therefore, for the purpose of this study, a target sample size of 500 patients will be recruited. It is expected that 15% (*n* = 75) will be low/average risk for melanoma, 50% (*n* = 250) will be moderate/high risk, and 35% (*n* = 175) will be very high risk. The majority of the patients will have up to six sequential TBP captures, taken at intervals of every 6 to 12 months. From each TBP capture, an average of 500 image tiles (8 cm × 10 cm) will be produced, annotated and available for development of the photodamage CNN algorithm.

Over a 2 years period, considering the melanoma incidence in Queensland (Australia) (15), we anticipate incidence rates of 0.3, 1.2, and 2.8% for individuals classified under low/average risk, moderate/high risk, and very high risk, respectively. Therefore, we expect 8 annotated melanomas (*n* = 0.2, *n* = 3, *n* = 5 in sequence). Correspondingly, it is expected that there will be 67 keratinocyte cancers for every melanoma diagnosed (16). Therefore, we expect 549 keratinocyte cancers (13 in the low/average risk group, 201 in the moderate/high risk group and 335 in the very-high risk group).

With respect to benign lesions, the median general population total body nevus counts >2 mm in diameter in the Queensland general population are 32 nevi per person (17). Higher counts are expected for those at higher risk of melanoma with a median number of nevi >2 mm in diameter reported in a Swiss cohort at 189 per person (18). We therefore conservatively estimate those at moderate/high risk to have a median around 80 nevi >2 mm in diameter. Hence, a total of approximately 66,475 nevi (2,400, 20,000, 33,075 respectively) will be annotated across 500 individuals at one time point. We estimate a ratio of 1:4 for nevi:other benign lesions (19), and therefore estimate an additional 265,900 other benign lesions for annotation.

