### Data anonymization

#### Image anonymization

To effectively anonymize the 3D TBP images for annotation, the original 2D macro images are divided into small tiles of approximately 8 cm × 10 cm, padded with a 5% overlap in each direction, to ensure coverage of all lesions. For each tile, a set of tile masks are also produced representing (a) the unique regions of the tile for which the tile has the best (most orthogonal) view of those regions, (b) the area of the tile excluding any padding, and (c) the initial AI-based lesion detection produced by the VECTRA WB360 (13). Average resolution and primary anatomic location are also recorded for each tile. Anatomic location is specified as one of ten categories: Torso (front & back), Left & Right Arm (Upper & Lower), Left & Right Leg (Upper & Lower).

For further anonymization, the patient’s face and head are automatically identified and masked out in any tile. Tools are also available to paint any additional areas that may be identifiable, such as tattoos.

The tile masks, lesion auto-detection, and associated metadata are saved for direct uploading to the annotation software, *Darwin* platform (V7 Labs, London, United Kingdom). Sufficient metadata on each tile are recorded so that any later annotation on the tiles can be mapped back to the 3D TBP avatar image.

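### The stated training/validation/test split is by image tile with no patient grouping, so followed as written it does not give the unseen test set it claims

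*Protocol article*

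**What the plan says.** The Data splitting section names the object that is divided: "The annotated image tiles are divided into three distinct datasets (training, validation, and test datasets), for AI-based model development and evaluation process". The method is stratified randomisation with "65% of the data allocated to the training set, 20% to the validation set, and the remaining 15% to the test set". One stratification factor is given: "Stratification is used to ensure all diagnostic classes (Table 1) are sufficiently represented in each dataset". The purpose of the third set is that models are "ultimately tested on unseen data (test set) to estimate its real-world performance accurately".

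The Primary objective section adds only that "This master dataset will be partitioned to create separate training, test, and validation datasets", without naming a unit. No section says that the tiles, captures or lesions of one patient are kept together.

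Other sections show how the tiles relate to each other:

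- Sample size: "a target sample size of 500 patients will be recruited", each capture gives about 500 tiles on average, and "The majority of the patients will have up to six sequential TBP captures, taken at intervals of every 6 to 12 months".
- Image anonymization: tiles are "padded with a 5% overlap in each direction, to ensure coverage of all lesions".
- Inter-exploration lesion matching: one lesion can be visible in several views.
- Lesion change detection: the same lesion is deliberately matched from one capture to the next.

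**The concern.** Tiles from one person share skin tone, sun damage, nevus pattern, lighting and pose. Tiles of one site from successive captures show the same lesions. If tiles are randomised without regard to patient, the test set consists of other pictures of the people the model was trained on. It then measures performance on new images of known patients. The tools are meant for patients the model has not met, and the Discussion foresees triage use by non-dermatologists.

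Two results are at stake. One is the test performance of the trained detection and classification models. The other is model choice: the validation set used for tuning has the same overlap, and the Skin lesion classification section leaves the EfficientNet variant to be chosen by experiment.

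This goes beyond detail that a condensed article leaves to a fuller document. The article states a unit and a stratum and then claims a property that they do not deliver.

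**Working it through.** **Inputs.** Allocation p = (0.65, 0.20, 0.15) from Data splitting. From Sample size: 500 patients, about 500 tiles per capture, up to six captures, and 8 expected melanomas.

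**The plan's own figures.** 65 + 20 + 15 = 100%. One time point gives 500 × 500 = 250,000 tiles, which split into 162,500, 50,000 and 37,500. The melanoma count reproduces: 75 × 0.003 + 250 × 0.012 + 175 × 0.028 = 0.225 + 3.0 + 4.9 = 8.1, stated as 8.

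**Assumption.** Images of one patient or lesion are allocated independently with probabilities p. Stratifying by class makes this approximate. The approximation is close for common classes and weaker for very rare ones.

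**Patients.** With 500 tiles from a single capture:

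- P(no test tile) = 0.85^500 ≈ 5e-36
- P(no validation tile) = 0.80^500 ≈ 4e-49

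So effectively all 500 patients are in all three sets. The result does not depend on the full 500 tiles. The probability of being in all three sets is 1 − (0.35^k + 0.80^k + 0.85^k) + (0.65^k + 0.20^k + 0.15^k), which is already 95.0% at k = 20 tiles and 99.97% at k = 50.

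**Lesions.** For a lesion shown on k annotated images:

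- P(a test image has at least one training sibling) = 1 − 0.35^(k−1)
- P(lesion in more than one set) = 1 − (0.65^k + 0.20^k + 0.15^k)
- P(lesion in all three sets): the formula above

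| k | Test image has a training sibling | Lesion in more than one set | Lesion in all three sets |
|---|---|---|---|
| 2 | 65.0% | 51.5% | 0% |
| 3 | 87.8% | 71.4% | 11.7% |
| 6 | 99.5% | 92.5% | 43.4% |

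A lesion on a single tile is in one set only, but its patient is still in all three.

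**Split by patient.** 500 × p = 325/100/75 patients, with no patient or lesion shared between sets. Expected melanomas are 8 × p = 5.2/1.6/1.2. If the 8 melanomas are in 8 different patients and allocation is not stratified, P(none in test) = 0.85^8 = 27% and P(none in validation) = 0.80^8 = 17%.

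**The case against.** The strongest reply is that a patient-grouped split also divides tiles into three sets. The text speaks of 65% of the data, gives no explicit unit for the randomisation and never says that class is the only stratum. Grouping by patient may be what is done in practice. This stands as a limit: the article does not show that patients have in fact been split across sets. It does show that the only unit named is the tile, that no grouping is stated and that an unseen test set is claimed. If grouping is already applied, one sentence corrects the text.

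Several stronger readings are tempting, but the documents do not support them:

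- *Every lesion falls in all three sets.* The table contradicts this: 43.4% at six images, 11.7% at three and none at two.
- *99.5% is the typical figure.* It is a ceiling. Six captures is a maximum and no distribution is given. The nevus total is stated for one time point, and the tile count per capture is tied to the photodamage algorithm. If diagnostic labels cover one time point only, lesion overlap across captures does not arise for the classifier. Patient overlap remains.
- *Overlapping tiles are a main source of duplication.* Within a capture, the best-view masks, the marking of invalid areas (Figure 2 legend) and the single best-view crop per lesion largely limit it.
- *Every test figure is inflated.* The segmentation step relies on a pretrained model, and no fine-tuning of it is described. Ugly-duckling scoring compares lesions within one capture, so overlap could enter only through the classifier's features. Nothing says that the patient-risk model is trained or split on tiles.
- *Confidence intervals will be too narrow.* The article states no interval method, so there is none to criticise.

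**Conclusion.** The rule is wrong as written. It names tiles, gives diagnostic class as the stratum and states no patient grouping, so it does not yield the unseen test set it promises. Overlap of patients is practically certain under the rule, even with far fewer than 500 tiles each. Overlap of lesions depends on how many captures are annotated, and the article does not settle that.

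The expected direction is optimism for new patients, in the test results of the trained detection and classification models and in choices made on the validation set. Its size cannot be computed, because the article gives no within-patient correlation. The primary objective, building the database, is not affected. The secondary objectives that rest on trained models are. The conclusion assumes that the stated rule is followed literally and that allocation is close to independent within patients.

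**What to change.** State in Data splitting that the unit is the patient. All tiles, captures and lesion crops of a patient go to one partition, about 325/100/75 patients. Use the same partition for every algorithm, and stratify it by risk group and by presence of rare diagnoses. Use patient-grouped cross-validation for the rare classes, because one test set cannot carry them. Any intervals reported should be clustered by patient.

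The text change is small, but three costs should be stated:

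- Reported accuracy will probably be lower.
- Any model already trained on a tile split must be re-run, so the correction should come before test results are released.
- The test set will hold about one melanoma. Stratification reduces the 27% risk of having none but does not add cases. A tile split does not escape this: 15% of 8 distinct melanomas with one image each is also 1.2.

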**Conclusion:**

The anticipated results from this protocol are validated AI-based tools to provide holistic risk assessment for individual lesions, and risk stratification of patients to assist clinicians in monitoring for skin cancer.

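### With 8 melanomas expected in all, the 65/20/15 split leaves about one in the test set, too few to estimate melanoma performance

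*Protocol article*

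**What the plan says.** The Sample size section explains that no formal calculation was made and that "a target sample size of 500 patients will be recruited". These are 75 low/average-risk, 250 moderate/high-risk and 175 very-high-risk patients. For a two-year period it states that "we anticipate incidence rates of 0.3, 1.2, and 2.8% for individuals classified under low/average risk, moderate/high risk, and very high risk, respectively", and concludes: "Therefore, we expect 8 annotated melanomas". It also expects 549 keratinocyte cancers.

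The Data splitting section takes the annotated image tile as the unit and uses stratified randomisation, with "65% of the data allocated to the training set, 20% to the validation set, and the remaining 15% to the test set". It gives the reason: "Stratification is used to ensure all diagnostic classes (Table 1) are sufficiently represented in each dataset". The validation set is for tuning, and the test set is for an accurate estimate of performance in practice.

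Table 1 lists melanoma (MM) as a class of its own, separate from suspicious melanocytic lesion (SM). The Skin lesion classification section trains a multi-class classifier on the Table 1 classes. The Lesion risk assessment section feeds the resulting diagnosis into the lesion risk score. Among the anticipated results, the Abstract lists "validated AI-based tools to provide holistic risk assessment for individual lesions".

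**The concern.** The two sections do not fit together for melanoma. Stratification reproduces the class proportions of the whole dataset in each part; it does not add cases of a rare class. A class with 8 members can be present in all three sets, but it cannot be numerous enough in a 15% test set for the purpose the article gives that set.

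What is at stake is melanoma sensitivity, a central property of a tool whose stated aim is melanoma risk assessment. It would be read off about one lesion, and tuning with respect to melanoma would rest on one or two. The article describes no external melanoma cases for testing the classifier, no cross-validation and no merging of rare classes. The public dermoscopy images it mentions are used only to fine-tune the super-resolution model.

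**Working it through.** **Inputs.** Group sizes 75, 250 and 175; two-year incidence 0.3%, 1.2% and 2.8%; 549 keratinocyte cancers; up to six captures per patient at 6- to 12-month intervals (all from Sample size). Split fractions 0.65, 0.20 and 0.15 (Data splitting).

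**Step 1. Reproduce the expected number of melanomas.** Sum of group size × incidence:

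75 × 0.003 + 250 × 0.012 + 175 × 0.028 = 0.225 + 3.0 + 4.9 = 8.125.

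This agrees with the stated 8, counting one melanoma per affected person.

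**Step 2. Apply the split.**

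| Set | Fraction | 8 × fraction | Whole lesions |
|---|---|---|---|
| Training | 0.65 | 5.2 | 5 |
| Validation | 0.20 | 1.6 | 2 |
| Test | 0.15 | 1.2 | 1 |

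**Step 3. Precision of sensitivity in the test set.** For n of n correct, the exact (Clopper-Pearson) 95% lower limit is 0.025^(1/n) and the upper limit is 100%.

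- n = 1: 1/1 gives 2.5 to 100%; 0/1 gives 0 to 97.5%.
- n = 2: 2/2 gives 15.8 to 100%.
- n = 3: 3/3 gives 29 to 100%.

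**Step 4. Does the result depend on the figure of 8?**

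- Chance variation: the 95% range of a Poisson count with mean 8.125 is 3 to 14. Times 0.15, this is 0.45 to 2.1 test melanomas.
- All 500 patients at the very-high-risk rate (assumption): 500 × 0.028 = 14, and 14 × 0.15 = 2.1.
- Incidence accruing over the whole span of six captures (assumption): five intervals of 6 to 12 months are 2.5 to 5 years. 8.125 × 2.5/2 = 10.2 and 8.125 × 5/2 = 20.3, giving 1.5 to 3.0 test melanomas.
- Every melanoma visible in all six captures (assumption, an upper bound): 8 × 6 = 48 images, and 48 × 0.15 = 7.2 in the test set, still from at most 8 distinct lesions.

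In none of these cases does the expected number of independent test melanomas exceed about 3.

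**Step 5. For scale.** A 95% interval of ±10 points needs s(1 − s) × (1.96/0.10)² test melanomas. At an assumed sensitivity of 90% this is 0.09 × 384.16 = 34.6, about 35. At 80% it is 0.16 × 384.16 = 61.5. Dividing by 0.15 gives roughly 230 to 410 melanomas in total, against 8.

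**Step 6. What using all 8 would give.** If each melanoma is predicted once out of sample, 8/8 gives 63 to 100% and 7/8 gives 47 to 99.7% (exact 95%).

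**Step 7. Comparison class.** Keratinocyte cancers: 549 × 0.15 = 82 in the test set, before dividing them between BCC and SCC, for which the article gives no separate counts.

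**The case against.** The strongest reply is that the article never defines sufficient representation. A 5/2/1 allocation puts melanoma in every set, so the statement is not literally false. That stands as far as presence goes. It does not meet the purpose the same section states for the test set, which one lesion cannot serve.

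A second reply is that the unit of the split is the tile, and repeat captures and tile overlap can raise the number of melanoma tiles above 8. That is also true, but they are further pictures of the same lesions, not independent cases. The article mentions no grouping by patient, so a tile-level split could also place one lesion in both training and test sets.

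Third, the primary objective is to build a database, and the classifier is a secondary objective. The Abstract also presents validated tools as an anticipated result rather than a demonstrated one. This limits the consequence: the dataset is not invalidated by the split.

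A reader might infer more than the documents support:

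- *That rare classes fail in general.* The article gives counts that show a shortfall for melanoma only. Keratinocyte cancers are adequate in aggregate, and there are no expected counts for classes such as SM, dermatofibroma or collision tumour.
- *That the test set may well contain no melanoma.* Such a probability assumes a split not stratified on diagnosis, whereas the article stratifies on it.
- *That the remark about preventing class imbalances is wrong.* It can be read as imbalance between the sets, which stratification does address.
- *That a high overall accuracy would conceal the failure.* This needs a benign-versus-malignant collapse that the article does not define for its 14-class classifier, and the article does not name overall accuracy as the classifier's metric.

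**Conclusion.** The point holds for melanoma. On the article's own figures, about one distinct melanoma reaches the test set and one or two reach the validation set. Sensitivity from one lesion has an exact 95% interval about 97 points wide whichever way it falls. The sufficiency claim, and the claim that the test set estimates real-world performance accurately, are therefore unsupported for this class.

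The conclusion rests on the planning figure of 8, on lesions rather than tiles as the independent unit, and on no outside melanoma cases being added for testing, since none is described. Labels given on image appearance could differ in number from incident cases, but 8 annotated melanomas is the figure the article plans on. The documents do not support the wider conclusion that the split is unsuitable for every class or that the dataset itself is compromised.

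**What to change.** 1. Split by patient rather than by tile, so that all captures of one lesion stay together.
2. For the melanoma class, replace the single hold-out by patient-grouped cross-validation, for example with five folds. Each melanoma is then predicted once by a model that never saw that patient.
3. Keep a locked 15% patient-level test set for the common classes, with melanoma patients left out of it. Otherwise a patient in the locked set would also enter training folds.
4. Report melanoma sensitivity with an exact interval.
5. State the expected melanoma counts per set (about 5/2/1 under the present split), and withdraw or qualify the sufficiency and accuracy claims for melanoma. Say plainly that the cross-validated estimate also stays imprecise (63 to 100% even if all 8 are correct) and does not by itself support validated melanoma performance.

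Pooling all malignant lesions into one target is not a substitute. Melanoma would be 8 of 8 + 549 = 557 cancers, or 1.4%, and its sensitivity would disappear in the total.

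**Cost.** With five folds, about five times the classifier's training compute, some changes of text and a more modest claim for melanoma. No extra patients are needed.

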#### Lesion detection and segmentation

For this task, a three-step approach is used to tackle lesion detection and segmentation. Given that image tiles may include background other than skin, images are pre-processed to obtain a corresponding skin mask. This is achieved by applying image thresholding within the HSV (hue, saturation, value) color space, followed by the application of morphological operations to enhance and clean the segmentation result. The resulting skin mask is applied to the final lesion segmentation, to eliminate the inaccurate detections (outside the skin region).

For lesion detection, the YOLO (You Only Look Once) model is employed (27), customized for our specific dataset. To expedite the model’s convergence and improve its performance, the training process is initialized using pre-trained weights on the COCO (Common Objects in COntext) dataset (28). This approach leverages the knowledge and features learned from a broader dataset and fine-tunes the model for our dataset. By initializing with pre-trained weights, the model is built on a solid foundation and already possesses an understanding of basic object features, allowing it to adapt more efficiently to our data. This transfer learning strategy not only accelerates the training process but also often leads to better performance compared to training from scratch, particularly when working with limited data.

The bounding box predictions provided by the lesion detection model are used as initial prompts for subsequent instance segmentation, for which we leverage the Segment Anything Model (SAM) (29) performance. SAM is a state-of-the-art instance segmentation model known for its accuracy and robustness. Its impressive zero-shot performance, often comparable to or better than fully supervised models, highlights its versatility and potential for various applications. An example of the results of this three-step approach is presented in Figure 3.

